#### Follow-up

Clinical consultations with the treating radiation oncologist including physical examination will be performed yearly from BCS to 5 years after single-dose RT, and every other year from 6 to 10 years. During the consultation, toxicity and cosmetic outcome will be assessed by the radiation oncologist (Fig. 1). Questionnaires on quality of life, distress, and cosmetic outcome questionnaires will be filled out by the patient. Digital photographs for objective evaluation of cosmetic outcome will also be taken at 3, 5, and 10 years after RT. As per standard of care, radiological follow-up will consist of yearly mammograms in the first 5 years. After 5 years, additional mammograms will be performed at 6, 8, and 10 years after RT.

### Biobank

The diagnostic biopsy, the surgical specimen, and blood samples will be preserved for 25 years at the Amsterdam UMC Central Biobank, location VUmc for future research in the field of breast cancer if patients give additional consent. To evaluate the radiation effect on gene expression in the breast tumor, additional consent for gene expression profiling is obtained. Since the tissue volume of the diagnostic biopsy is too little for gene expression profiling, 2–3 extra 14G tumor biopsies are taken after additional informed consent by the patient. RNA is easily degraded during the process of formalin fixation and a large variety exists due to different protocols used for fixation [35, 36]. Therefore, fresh frozen biopsies are used for gene expression profiling with RNA.

### Ethical aspects

This study is conducted according to the Declaration of Helsinki (Fortaleza, Brazil, October 2013) and the Dutch Medical Research Involving Human Subjects Act (http://www.ccmo.nl). The study protocol has been approved by the Medical Research Ethic Committee of the Amsterdam UMC, location VUmc (NL77000.029.21), and has been registered at an international trial registry (ClinicalTrial.gov: NCT05350722). The study has been approved by the Institutional Review Board of each participating center. After a written and oral explanation of the study, all patients are required to give written informed consent before inclusion.

### Quality assurance

To assure the quality and validity of the research data, an independent qualified monitor will carry out study monitoring centrally at the Clinical Monitoring Center of the Amsterdam UMC, location VUmc. The monitoring will be performed according to national guidelines on quality control for Dutch University Medical Centers [37].

### Statistical analysis

Sample size calculation is performed based on the primary endpoint: the rate of pathologic complete response. We expect that 40% of our patients will achieve pathologic complete response 12 months after high-dose single fraction PBI. The sample size calculation is performed using the Wilson method for the calculation of different 95% confidence intervals (CI) for proposed sample sizes. A sample size of 100 patients would produce an acceptable 95% CI ranging from 30.9% to 49.8% while maintaining practical applicability.

The proportion of patients with pCR 12 months after RT will be evaluated and a 95% CI will be calculated. Regarding the secondary outcome, radiologic response, the negative and positive predictive value of radiologic response for pCR with 95% CIs will be calculated for all intervals between RT and BCS. Patient-reported and cosmetic outcomes will be analyzed in a linear mixed model for repeated measures. Radiation- and surgery-induced toxicity, local, regional and distant relapse rates, disease-free and overall survival will be reported using descriptive statistics. Kaplan–Meier method will be used to quantify disease-free and overall survival. The natural variability of the response markers will be evaluated for all accrued patients, exploring overlap in variance among the different response markers, and if applicable studying the reproducibility of the potential response markers.

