## Methods/design

### Study design

The ABLATIVE-2 trial is a Dutch multicenter, phase II, single-arm prospective study at the Radiotherapy Departments of the Amsterdam University Medical Centres (UMC) and Radboudumc in the Netherlands. Eligible patients are treated with MR-guided pre-operative PBI. BCS will be performed at 12 months post-PBI. Between RT and surgery, tumor response is monitored using MRI at 2 weeks, 3, 6, 9 and 12 months, and compared with the baseline MRI (before PBI). In case of tumor progression on MRI at any time or when residual tumor at 6 months is suspected, BCS is performed immediately (within two to four weeks). The primary objective of this study is to determine the rate of pCR one year after single-dose ablative RT and BCS in patients with early-stage breast cancer. The secondary objectives are to evaluate the radiologic response on MRI, radiotherapy- and surgery-induced toxicity, cosmetic outcome, and patients’ quality of life and distress. The oncological outcomes: local, regional, and distant relapse rates and overall survival will be assessed. Liquid biopsies and immune response markers in blood and tumor tissue pre- and post-RT will be evaluated. All tumor tissue and blood samples of patients will be preserved at the Amsterdam UMC Central Biobank, location Vrije Universiteit Medical Center (VUmc).

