### Study outcomes

The primary endpoint is the rate of patients with pCR one year after single-dose pre-operative RT treatment. Secondary endpoints are the time to rCR on MRI and the correlation between radiologic and pathologic response. In addition, radiotherapy- and surgery-induced toxicity will be assessed according to the Common Toxicity Criteria Adverse Events version 5.0 [32]. Patient-reported outcome measures will be assessed using the European Organization for Research and Treatment of Cancer core-30 (EORTC-QLQ-C30) and breast cancer-specific (QLQ-BR23) quality of life questionnaires and the Hospital Anxiety and Depression Scale (HADS) questionnaire. Cosmetic outcome is assessed by the patient using the BREAST-Q questionnaire. The radiation oncologist rates the cosmetic outcome as excellent, good, fair, and poor, based on breast changes such as telangiectasia and fibrosis. Cosmetic evaluation is also performed objectively using imaging captured by the VECTRA XT 3D-imaging system (Canfueld Sci, New Jersey, USA). Oncological outcomes are assessed using local, regional and distant relapse rates, and disease-free and overall survival since RT. Additionally, liquid biopsies and radiotherapy-associated immune response markers in blood and pre- and post-RT tumor tissue are investigated. The time points for the evaluation of outcomes are displayed in Fig. 1.

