**Fig. 1 Fig1:**
[figure not shown]
Overview of outcome measurements. Time points counted from radiotherapy treatment. Legend: w weeks, m months, y years. *questionnaires include evaluation of cosmetic outcomes and quality of life

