#### Follow-up after single-dose ablative treatment

Frequent clinical and radiological evaluation will be performed after single-dose PBI at 2 weeks, 3, 6, 9, and 12 months. Tumor response will be classified according to the ‘Response Evaluation Criteria in Solid Tumors’ guidelines [33]. Radiologic complete response on MRI is defined as the complete absence of pathologic contrast enhancement and complete absence of pathologic apparent diffusion coefficient reduction in the original tumor bed. Additionally, at baseline and during each follow-up consultation (i.e. at 2 weeks, 3, 6, 9, and 12 months) blood samples will be taken.

Patients with an indication for endocrine therapy will start this treatment following RT. The treating medical oncologist will monitor the endocrine treatment. If the surgical specimen shows any microscopic findings resulting in an indication for the start or change of adjuvant systemic therapy according to the Dutch national guidelines, patients will be treated accordingly [34].

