#### Breast-conserving surgery

To assess the effect of RT on the breast tumor, BCS is performed at 12 months following RT. BCS will be performed ahead of time in case radiologic tumor progression (an increased size of contrast enhancement) is observed, or in case the MRI does not show rCR at 6 months following RT.

The surgical specimen is evaluated by a dedicated breast pathologist at the hospital where the surgery is performed. Viable tumor cells will be evaluated using hematoxylin and eosin staining and the activity of cytokeratin antibodies. Pathologic response will be categorized according to the European Society of Mastology (EUSOMA criteria).1. Complete pathologic response is defined as either no residual carcinoma or no residual invasive carcinoma but ductal carcinoma in situ (DCIS) may be present.2. Partial response to therapya. Near complete response is defined as minimal residual disease (<10% tumor cells)b. Evidence of response (10-50% tumor cells)c. >50% tumor cellularity remains evident with features of response present (e.g. fibrosis)3. No evidence of response

In addition, the proportion of patients with DCIS in the surgical specimen will be recorded. The surface of the excision specimen will be marked with Indian ink to evaluate surgical margins. Surgical margins will be described as minimal microscopic tumor-free margins of invasive and in situ carcinoma in millimeters (mm). This will always be performed in the direction of the nearest surgical margin. If tumor-positive margins are found, a radical re-excision needs to be performed.

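### The linear mixed model planned for all cosmetic outcomes does not suit the radiation oncologist's four-category rating

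*Protocol article*

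**What the plan says.** The Statistical analysis section of the protocol article assigns methods by type of outcome. Toxicity and relapse rates are summarised descriptively, and disease-free and overall survival also get the Kaplan–Meier method. For the remaining outcomes at issue here, "Patient-reported and cosmetic outcomes will be analyzed in a linear mixed model for repeated measures".

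The Study outcomes section names three cosmetic measures:

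- a patient measure: "Cosmetic outcome is assessed by the patient using the BREAST-Q questionnaire";
- a physician measure: "The radiation oncologist rates the cosmetic outcome as excellent, good, fair, and poor";
- an objective measure from 3D imaging.

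The quality-of-life and distress instruments are the QLQ-C30, QLQ-BR23 and HADS. Nothing in the article takes the physician rating out of the linear model or gives it a method of its own.

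**The concern.** The physician rating has four ordered categories and no natural distances between them. A linear mixed model needs a number for each category, for example 4 for excellent down to 1 for poor. It then assumes that a step from excellent to good equals a step from fair to poor, and that ratings vary normally around their mean with no upper limit.

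The Background reports good to excellent physician ratings in 89–100% of patients in earlier studies of pre-operative irradiation, so ratings may pile up at the top of the scale, where these assumptions are weakest.

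The second issue is what gets reported. The article gives cosmetic results of pre-operative irradiation as the percentage good or excellent (Background and Discussion). A mean score from a linear model cannot be set beside those percentages, and two quite different sets of ratings can share one mean.

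**Working it through.** **The plan's own figure.** The only calculated design figure is the Wilson 95% interval for a 40% response rate in 100 patients. With z = 1.96 the score interval is 30.9% to 49.8%, as stated. It concerns the primary endpoint and does not depend on this point. The article gives no figure for the mixed model.

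**Inputs.** Four ordered categories (Study outcomes). Good or excellent by physicians: 89–100% (Background), and 62% in one trial of 22 patients (Discussion). The article does not give the split over all four categories, so the distributions below are assumptions chosen to match those totals.

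**Check 1: how well a normal model fits the scale.** Score excellent = 4, good = 3, fair = 2, poor = 1. For shares p(x):

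- mean m = Σ x·p(x)
- SD s = √Σ (x − m)²·p(x)
- share implied above the top category = 1 − Φ((4 − m)/s)
- upper 95% reference limit = m + 1.96·s

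First row: m = 0.60×4 + 0.29×3 + 0.09×2 + 0.02×1 = 3.47; s² = (9.60 + 2.61 + 0.36 + 0.02) − 3.47² = 0.549, so s = 0.74; (4 − 3.47)/0.741 = 0.715, so the share above 4 is 23.7%; upper limit 3.47 + 1.96×0.741 = 4.92. The other rows follow in the same way.

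| Excellent/good/fair/poor (assumed) | Good or excellent | Mean | SD | Skew | Implied above 4 | Upper limit |
|---|---|---|---|---|---|---|
| 60/29/9/2% | 89% | 3.47 | 0.74 | −1.3 | 23.7% | 4.92 |
| 50/39/9/2% | 89% | 3.37 | 0.73 | −1.0 | 19.4% | 4.80 |
| 70/25/4/1% | 95% | 3.64 | 0.61 | −1.7 | 27.7% | 4.83 |
| 80/20/0/0% | 100% | 3.80 | 0.40 | −1.5 | 30.9% | 4.58 |
| 25/37/28/10% | 62% | 2.77 | 0.94 | −0.3 | 9.5% | 4.61 |

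In the 89–100% range, 19–31% of the implied ratings lie above the best category. At 62% the skew is slight and the overshoot smaller. These percentages describe individual ratings implied by the model. An estimated visit mean would normally stay between 1 and 4.

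**Check 2: whether the mean carries the percentage.**

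- 60/32/6/2%: mean = 2.40 + 0.96 + 0.12 + 0.02 = 3.50; good or excellent = 60 + 32 = 92%.
- 70/15/10/5%: mean = 2.80 + 0.45 + 0.20 + 0.05 = 3.50; good or excellent = 70 + 15 = 85%.

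The means are equal and the percentages differ by 7 points. This is a constructed case: excellent rises by 10 points while fair or poor rises by 7. If all ratings shifted in one direction, the mean would shift too. It shows that the mean does not determine the percentage, not that such a pattern is expected.

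**The case against.** The strongest reply is that little is at stake. The rating is one of several secondary outcomes in a single-arm trial. With up to 100 patients a visit mean is roughly normal even if individual ratings are not, and the percentage good or excellent can be tabulated from the same data. The example with equal means is invented, and the 62% figure shows that ceiling bunching is not certain. All of this stands and limits the severity. It does not remove the mismatch: the article names a method for this outcome, the method does not suit the scale, and a tabulation beside the model would leave the stated analysis answering a different question. Because the method is stated, this is not a detail left to the full protocol or analysis plan.

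Two stronger readings are tempting.

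- A reader might infer that a single model is to cover all these outcomes together. The wording more naturally means one type of model, fitted to each outcome, and that type is reasonable for the questionnaire scores.
- A reader might infer that means by time since radiotherapy will mix operated and unoperated patients between about 7 and 12 months. The caption of Fig. 1 says "Time points counted from radiotherapy treatment". Planned surgery is at 12 months, but it is brought forward "in case the MRI does not show rCR at 6 months following RT", or on progression. Solving 0.42 = PPV·r + (1 − NPV)·(1 − r) for the share r with radiologic complete response, with the Background's PPV of 67–88% and NPV of 76–85%, leaves 48–72% without it (if those 6–8-month data apply at 6 months). The timing difference is real, but the documents do not show a flawed analysis. The caption describes when measurements are taken, not the model's time variable. The article neither includes nor excludes a surgery term, a detail commonly left to the full protocol or analysis plan. The schedule of questionnaires and cosmetic ratings is in a figure that is not shown; the text on evaluations up to 12 months does not mention these outcomes, and the later Follow-up section places them at consultations from surgery onward.

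**Conclusion.** The concern holds for the radiation oncologist's rating alone. The planned linear mixed model does not suit a four-level ordinal scale and does not deliver the percentage good or excellent that the article uses for comparison. The misfit is marked if ratings resemble the 89–100% of most earlier studies (19–31% of implied ratings above the scale) and milder if they resemble the 62% trial (about 9%). These sizes rest on assumed category splits. The conclusion that the scale is ordinal does not.

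Severity is minor. The BREAST-Q, QLQ-C30, QLQ-BR23 and HADS analyses, the pathologic complete response estimate and the sample size are unaffected. Neither a single joint model nor mixing by surgical status is part of the finding.

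**What to change.** State a separate analysis for the physician rating:

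- Use a cumulative-logit mixed model with a patient random effect, or a logistic mixed model or GEE for good or excellent against fair or poor.
- Report the percentage good or excellent at each visit with a 95% confidence interval. The Wilson method used in the sample size section would serve.
- Keep the linear mixed model for the BREAST-Q, QLQ-C30, QLQ-BR23 and HADS scores.

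The cost is a sentence or two in the plan and slightly more analysis; data collection does not change. Sparse categories are the main difficulty: at 89% good or excellent, 100 × (1 − 0.89) = 11 of 100 patients would be fair or poor, and at 100% none would be. Fair and poor may then need merging, by a rule set in advance. The ordinal model has the advantage that it still uses the split between excellent and good. GEE without weighting makes a stricter assumption about missing visits than the mixed models do, which matters with follow-up to 10 years.

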## Discussion

The ABLATIVE-2 study is a continuation of the ABLATIVE study (NCT02316561) in which 36 patients were treated with a single ablative RT dose and BCS at 6 or 8 months following RT. This study showed that single-dose pre-operative PBI was technically and clinically feasible in patients with low-risk breast cancer [21]. The pCR rate after 8 months between RT and BCS seemed to be higher than after 6 months (48% vs. 33%). Therefore, in the current ABLATIVE-2 design, the interval between RT and BCS is prolonged to 12 months. In addition, the predictive value of quantitative MRI parameters and immunological markers, and potential biomarkers in blood and tumor tissue for pCR will be evaluated.

Over the last decades, clinical research has been focused on personalized treatment aiming to de-escalate breast cancer treatment. In patients with early-stage breast cancer, BCS followed by WBI resulted in equivalent recurrence rates and overall survival compared with mastectomy [5, 38, 39]. In addition, axillary RT has replaced axillary lymph node dissection in patients with a tumor-positive sentinel node [40]. Genomic tools are utilized to identify low-risk patients with no benefit from chemotherapy [41, 42]. Irradiation times of breast cancer patients have been shortened with (ultra-) hypofractionated radiation schedules and treatment volumes have been reduced with accelerated PBI instead of whole breast irradiation in low-risk patients [11, 12, 43–46]. Thus, breast cancer treatment has become increasingly patient-tailored over the years.

Improved diagnostic modalities and treatment have led to a 15% decline in breast cancer mortality rates in Europe between 2002 and 2012 [47]. However, breast cancer patients seem to prefer treatments that result in less functional disability and pain over progression-free survival months [48]. As such, studies focusing on reducing radiation- and surgery-induced toxicity and improving the cosmetic outcome of personalized breast cancer treatment are increasingly performed. The introduction of pre-operative PBI has been gaining interest and has the potential to lead to a paradigm shift in the treatment of low-risk patients [17–23, 49]. PBI in the pre-operative setting has several advantages over post-operative treatment. Pre-operative tumor delineation is more accurate and leads to a reduced volume of irradiated healthy breast tissue, while still adhering to oncologically safe margins [13–15]. Precise irradiation could lead to milder toxicity and better cosmetic outcome [50]. The tumoricidal effect of irradiation can lead to tumor downstaging and preservation of breast tissue during surgical excision. In the ABLATIVE study an higher pCR rate of 42% was observed after a longer interval between pre-operative radiotherapy and surgery of 6 to 8 months [21]. In the PAPBI trial, 133 patients were treated with pre-operative PBI. Seventy-eight patients were treated with 40 Gy in 10 fractions in 2 weeks and 55 patients with 30 Gy in 5 fractions in 1 week [19]. BCS was performed 6 weeks after pre-operative PBI and a pCR rate of 10% was reported. IBTR was found in 3% of the patients after a median follow-up of 5 years and overall survival was 97%. The study by Nichols et al. included 27 patients, who received pre-operative PBI 10 × 3.85 Gy in 1 week [20]. After 3 weeks, pCR was achieved in 15% of the patients. Toxicity was mainly mild in this study and good to excellent cosmetic outcome was reported by 78% of the patients. Similar results were found in the ROCK trial. Twenty-two patients were treated with a pre-operative single-dose of 21 Gy using the Cyberknife® and BCS after 2 weeks [24]. Two patients (9%) experienced a pCR and no toxicity higher than grade 2 was reported. Cosmetic outcomes on the other hand were rated as good or excellent by 62% of the physicians. The SPORT-DS trial evaluated a pre-operative single-dose of 20 Gy and another retrospective cohort study evaluated a schedule with multiple fractions (3 × 9.5 Gy) followed by BCS after 3 and 6–8 weeks, respectively [17, 18]. These studies did not report a pCR in any of the patients, despite similar interval durations between PBI and BCS compared to the previously described studies. This difference could be explained by the small sample sizes.

The post-operative complication rate of BCS after pre-operative PBI is 14–17% [19, 21]. These complications include hemorrhage and wound infection. Analysis of 648 patients in the Cambridge IMRT trial, in which patients were treated with BCS followed by WBI, showed a post-operative infection rate of 19.7% and a hematoma rate of 7.9% [51]. Results of the study have proven that the presence of seroma is associated with post-operative infection and hemorrhage [52]. The FOCUS cohort study collected data on all consecutive patients aged 65 years and older with breast cancer in the Netherlands between 1997 and 2004 [53]. The post-operative complication rate for patients treated with BCS was 14%, which is similar to the patients treated with pre-operative PBI. In the ABLATIVE-2 trial, patients will have 12 months of recovery time until BCS is performed. So the negative effect of RT on the incidence of post-operative complications is expected to be minimalized.

Long-term outcomes of pre-operative PBI are awaited with the continuation of follow-up in these studies [17, 23, 54]. Continuation of patient accrual in the SPORT-DS trial will provide more information on tumor response rate in a larger study population (Table 3) [17]. The SIGNAL-2 trial (NCT02212860) will prolong the interval between RT and BCS from 1 to 3 weeks [22]. Based on the positive results of the previous phase I trial of Horton et al., a larger patient cohort will be treated with a single dose of 21 Gy at Duke University (NCT02482376) [23]. The optimal ablative dose has not yet been established, thus phase I dose-escalation trials (NCT04679454, NCT04040569) are recruiting patients to identify the maximum tolerated dose. The ABLATIVE-2 study is, to the best of our knowledge, the first study to evaluate the effect of pre-operative single-dose PBI after a longer interval, i.e. 12 months.

**Table 3 Tab3:** Summary of the clinical trial regarding pre-operative partial breast irradiation

Trial ID, status	Title	Treatment	Primary endpoints	Secondary endpoints	Estimated primary completion date
NCT05350722, recruiting	Single-dose Preoperative Partial Breast Irradiation in Low-risk Breast Cancer Patients (ABLATIVE-2)	Pre-operative single-dose radiotherapy (20 Gy) and BCS after 12 months	Pathologic complete response	Radiologic complete response, treatment-related adverse events, quality of life, cosmetic outcome, oncological outcomes, immune response and biomarkers	March 2025
NCT02913729, recruiting	Pre- Versus Postoperative Accelerated Partial Breast Irradiation (PAPBI-2)	Pre vs. post-operative PBI (5 × 5.2 Gy) and BCS 6 months after PBI	Cosmetic outcome	Pathologic complete response, postoperative complications	December 2022
NCT03917498, active/not recruiting	Single Pre-Operative Radiation Therapy—With Delayed Surgery for Low Risk Breast Cancer (SPORT-DS)	Pre-operative single-dose radiotherapy and BCS after 3 months^a^	Pathologic complete response	Radiation toxicity	February 28, 2020 (actual)
NCT02212860, active/not recruiting	Stereotactic Image-Guided Neoadjuvant Ablative Radiation Then Lumpectomy (SIGNAL 2)	Pre-operative PBI (21 Gy or 3 × 10 Gy) and BCS after 14–20 days	Immune priming, angiogenesis, proliferation/hypoxia/apoptosis/invasion markers, toxicity	Cosmetic outcome, survival	April 2021 (actual)
NCT03520894, recruiting	Radiotherapy in Preoperative Setting With CyberKnife for Breast Cancer (ROCK)	Pre-operative single-dose radiotherapy (21 Gy) and BCS after 30 days	Acute skin toxicity	Pathologic complete response, rate of complete resection, oncological outcomes, chronic toxicity, differential genetic expression, immune response and biomarkers	May 1, 2022
NCT04679454, recruiting	Single Fraction Preoperative Radiotherapy for Early Stage Breast Cancer (CRYSTAL)	Pre-operative single dose radiotherapy (18 Gy, 21 Gy, 24 Gy) and BCS after 4–8 weeks	Dose escalation, pathologic complete response	Chronic toxicity, cosmetic outcome, postoperative complications, oncological outcomes	March 2026
NCT03909282, recruiting	Phase 2 Surgical Excision vs Neoadjuvant Radiotherapy + Delayed Surgical Excision of Ductal Carcinoma (NORDIS)	Pre-operative PBI (5 × 6 Gy) and BCS after 3 months vs. upfront surgery	Rate of DCIS pathologic complete response	Wound complication, correlation of imaging characteristics and pathologic findings, rate of invasive carcinoma	September 2024
NCT04040569, recruiting	A Phase I Dose Escalation Study of Single Fraction Pre-operative Stereotactic Partial Breast Irradiation (S-PBI) for Early Stage Breast Cancer	Pre-operative single dose radiotherapy (30 Gy, 34 Gy, 38 Gy) and BCS^b^	Dose escalation, cosmetic outcome	-	September 2024
NCT02482376, active/not recruiting	Preoperative Single-Fraction Radiotherapy in Early Stage Breast Cancer	Pre-operative single-dose radiotherapy (21 Gy) and BCS^b^	Physician reported cosmetic outcome	Ki-67, patient reported cosmetic outcome, gene expression, local control, circulating cell free DNA	March 2025

*BCS* Breast conserving surgery, *PBI* Partial breast irradiation

^a^Dose not reported

^b^Timing of surgery not specified

The prediction of pCR using MRI will be challenging in the current study design. MRI will be performed at different time points after RT to evaluate tumor response. The MRI at 2 weeks in particular aims to identify early radiation effects. The parameter extraction from an MRI contains substantial variability across patients [55]. Therefore, reference objects, image acquisition protocols, and software for image data analysis need to be implemented. Hence, study results will have to identify other radiological predictors or tumor response markers in blood or tumor tissue to select good responders to RT.

A meta-analysis showed that the detection rates of ctDNA in blood samples of patients with early-stage breast cancer at baseline range between 23–100% [31]. Most studies included patients with triple-negative breast cancer, who have a higher ctDNA detection rate than patients with an ER + tumor [31, 56–58]. In patients with ER + early-stage breast cancer, ctDNA was detected in 24% of the patients (*n* = 51) [58]. However, the median ctDNA level, measured using personalized digital polymerase chain reaction assays, was 0 copies/ml in patients with a clinical T1 tumor. The detection of ctDNA in patients with early-stage breast cancer increases with deep sequencing using large gene panels. Zhang et al. prospectively collected plasma samples of 102 early-stage breast cancer patients and reached a positive detection rate of 74% (49/66) [56]. For patients with a clinical T1 tumor, the detection rate was 56%. Patients with a higher number (40–90%) of TILs were more likely to have ctDNA detection (92%) compared to patients with a low number (< 10%) of TILs (60%).

Similar to ctDNA detection, TILs levels are higher in triple-negative and HER2 + tumors [59, 60]. Still, in patients with luminal A breast cancer TILs have a prognostic value [61, 62]. The SweBCG91cRT trial has shown that patients with a Luminal A tumor and a low TILs score have a 51% reduced risk of IBTR when treated with post-operative RT compared to no post-operative RT [61]. In the ABLATIVE study, six to eight months after single-dose pre-operative PBI, a decrease of CD3, CD4, and CD8 TILs was found in tumor tissue [29]. However, no differences in TILs levels were found in responders vs. non-responders. Due to low TILs levels in luminal A tumors and subtle differences after treatment, analyzing a larger patient cohort will be necessary to predict pCR after single-dose pre-operative PBI using TILs.

Post-operative endocrine therapy is the standard of care for patients with an indication according to the Dutch guidelines. As surgery is scheduled 6 to 12 months after RT, endocrine therapy is allowed after RT (and before surgery) in this trial, despite possible tumor downstaging. The ABLATIVE-2 study has intensive MRI follow-up to monitor tumor response after pre-operative PBI and allows safe prolongation of the interval to BCS. In prospect, the number of MRIs could be reduced in case no disease progression is observed during the monitoring phase in this trial. In addition, the extensive diagnostic workup including a sentinel node procedure could be de-escalated, if favorable oncological outcomes are found in the current SOUND trial (Sentinel Node vs Observation After Axillary Ultrasound, NCT02167490) of the European Institute of Oncology in which the omission of the sentinel node procedure in clinically node-negative cT1 breast cancer patients undergoing BCS is investigated. This will make the clinical implementation of pre-operative single-dose PBI more practical. Nonetheless, MR-guided RT delivery is not common practice in most hospitals. The use of conventional and MR-linacs from different manufacturers could influence clinical outcomes of radiation treatment due to variations in the treatment protocols of the machines. The MR-linac provides an online adaptive workflow with good visibility of the breast tumor on MRI. This allows more precise treatment delivery and irradiation of smaller non-intended breast volumes reducing radiation-induced toxicity.

The ABLATIVE-2 trial is a multicenter prospective trial and contributes to the advancement of tailored breast cancer treatment with pre-operative single-fraction PBI in patients with low-risk breast cancer. If tumor response markers in blood or tumor tissue and radiological parameters are identified to successfully predict pCR in future patients, BCS could potentially be omitted in future low-risk patients. When a patient does not reach pCR after pre-operative single-fraction PBI, downstaging of the tumor could reduce excision volumes of healthy breast tissue and the number of RT fractions could be reduced to one single dose instead of the post-operative standard schedule of multi-fractionated RT for patients with early-stage breast cancer [43]. This could result in an overall reduction of treatment burden for patients and improve logistic challenges in healthcare.

